### Surveillance

#### Surveillance period and screening interval

After the patients are enrolled, US for HCC screening will be performed at 6-month intervals (6 times), and non-contrast liver MRI will be obtained at the 6th, 18th, and 30th months (3 times) during the 3-year follow-up period. At the 6-, 18-, and 30-month visit, US and non-contrast liver MRI will be performed on the same day. The US is to be performed earlier by an abdominal radiologist and immediately followed by a non-contrast MRI. The laboratory investigations will include α-fetoprotein (AFP) and protein induced by vitamin K absence/antagonist II (PIVKA-II) within one month of the image study date. Vital signs obtained in the outpatient clinic will be monitored by reviewing the electronic medical record. Each patient will be followed-up for approximately 36 months. Based on the last screening round of the last enrolled patient, the total duration of this trial will be approximately 4 years. The schedule of follow-up examinations is presented in Fig. 2.

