### Diagnostic work-up for HCC confirmation

If HCC is suspected on liver US or non-contrast liver MRI, a dynamic liver CT with 4 phases will be performed for confirmation. Imaging criteria of arterial hypervascularity and venous or delayed phase washout will be relied on to reach a diagnosis of HCC on dynamic liver CT [9]. If patients are diagnosed with HCC on dynamic liver CT, participation in the clinical trial will be terminated, and the patient will be immediately referred for treatment. If there is no evidence of HCC on dynamic liver CT, the patient will return to the regular surveillance schedule as outlined. If indeterminate lesions are identified on dynamic liver CT, liver MRI or biopsy will be considered. After the last surveillance round, patients with no suspicion of HCC or who have not been diagnosed with HCC during the 3-year follow-up period will be evaluated with a dynamic liver CT to exclude false-negative findings.

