### Endpoints

Primary endpoint: comparison of the HCC detection rate by US performed at 6-month intervals with that of yearly non-contrast liver MRI during a 3-year follow-up.

Secondary endpoint: survival of the patients who developed HCC during the 3-year follow-up period.

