### Statistical analysis

The sensitivity, specificity, positive predictive value, and negative predictive value of liver US and non-contrast liver MRI for the detection of HCC will be determined and compared. Detection rates and false referral rates will be evaluated. The difference in the detection rate of each modality will be compared using the McNemar test. A survival analysis of the patients who develop HCC during the study period will be determined according to the Kaplan-Meier method. A comparison of the survival curves will be made by means of the log-rank test. For continuous variables among clinical and demographic data, the mean, standard deviation, median, minimum, and maximum values will be presented. For comparison between patients with HCC or those without HCC during the study period, Student’s t-test will be used for continuous variables with a normal distribution, and Wilcoxon rank-sum test will be used for those with a non-normal distribution. A chi-square test will be used for categorical variables. Statistical analyses will be performed using SPSS, version 21.0 (IBM, New York, NY). *P-*value ≤0.05 will be considered indicative of a statistically significant difference.

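### HCCs confirmed at US-only visits leave the trial before their next MRI, so the per-patient McNemar comparison as worded counts them against MRI and can reverse the programme ranking

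*Protocol article*

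**What the plan says.** Four statements in the Protocol article bear on this point.

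- **Surveillance period and screening interval:** US is done six times at 6-month intervals, whereas "non-contrast liver MRI will be obtained at the 6th, 18th, and 30th months (3 times) during the 3-year follow-up period". The same section adds: "At the 6-, 18-, and 30-month visit, US and non-contrast liver MRI will be performed on the same day". Three of the six US rounds therefore have no MRI.
- **Diagnostic work-up for HCC confirmation:** "If patients are diagnosed with HCC on dynamic liver CT, participation in the clinical trial will be terminated". This applies whichever test raised the suspicion. Patients without a diagnosis at the end of surveillance "will be evaluated with a dynamic liver CT to exclude false-negative findings".
- **Endpoints:** the primary endpoint is "comparison of the HCC detection rate by US performed at 6-month intervals with that of yearly non-contrast liver MRI during a 3-year follow-up".
- **Statistical analysis:** "The difference in the detection rate of each modality will be compared using the McNemar test".

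The Discussion defends the yearly MRI interval as deliberate, with the longer gap offset by higher sensitivity. It does not say what happens when a patient leaves between two MRIs. The article also does not say how an HCC found at a US-only visit enters the paired table.

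**The concern.** The endpoint compares two surveillance programmes in the same patients, but each programme removes patients from the other. A tumour that US finds at a US-only visit is confirmed by CT and the patient leaves. The next scheduled MRI, which might also have found it, never takes place. Read per patient over three years, that tumour sits in the US-positive/MRI-negative cell. The closing CT cannot supply the missing reading, because the patient has already left.

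The reverse also happens: an HCC found only by MRI at a same-day visit ends the later US rounds. Neither programme is seen as it would run alone, and the McNemar contrast then reflects exit order as well as test performance. At stake is the direction of the primary result.

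**Working it through.** **Inputs from the plan.** Sensitivity is 60% for US and 80% for MRI, and cumulative HCC is 15% over 3 years with 192 evaluable patients (Sample size calculation). MRI is at months 6, 18 and 30, with exit at the first confirmed HCC. Expected HCCs: 0.15 x 192 = 28.8.

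**Assumptions, not in the text.**
- Onset is uniform over 36 months.
- US runs at months 6-36 or at 0-30.
- Misses are persistent (a tumour missed once by a tool is always missed by it) or independent between rounds.
- Detections are nested (every US-visible tumour is MRI-visible) or independent between tools.

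**The plan's own figure.** The closest match found for 192 is a McNemar calculation among HCC patients with one-sided alpha, 20% MRI-only and 0% US-only:

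(1.645 x √0.20 + 0.842 x √(0.20 − 0.04))² / 0.04 = 28.74, and 28.74 / 0.15 = 191.6, i.e. 192.

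The match therefore needs no US-only detections at all. (Two-sided, the same inputs give 245.)

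**Worked case: US at 6-36, persistent misses, nested.** Divide onset into six equal intervals, so that the first examination falls at month 6, 12, 18, 24, 30 or 36. Of the tumours, 60% are visible to both tools, 20% to MRI only and 20% to neither.

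- US alone: 60%.
- MRI alone: the first five intervals have a later MRI and the last has none, so 5/6 x 80% = 66.7%.
- As scored with exit, MRI: 80% where the first examination is at months 6, 18 or 30; 20% at months 12 or 24, because the US-visible 60% have left; 0 at month 36. (3 x 80 + 2 x 20 + 0)/6 = 46.7%.
- As scored, US: still 60%.
- US-only cell: (2 x 60 + 60)/6 = 30%, about 8.6 of 28.8. MRI-only cell: (5 x 20)/6 = 16.7%, about 4.8.

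MRI's fall from 80% to 46.7% has two parts. Tumours arising after month 30 account for 80 − 66.7 = 13.3 points. Exit at months 12 and 24 accounts for 66.7 − 46.7 = 20 points. Only the second part is an artefact.

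If detections are independent between tools, the 20% at months 12 and 24 becomes 0.4 x 80 = 32%, and scored MRI is (3 x 80 + 2 x 32)/6 = 50.7%.

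**Other cases** (no tumours prevalent at entry; ranges run over nested and independent tools):

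| US months | Misses between rounds | Stand-alone US / MRI, % | As scored US / MRI, % |
|---|---|---|---|
| 6-36 | persistent | 60.0 / 66.7 | 60.0 / 46.7-50.7 |
| 0-30 | persistent | 50.0 / 66.7 | 50.0 / 46.7-50.7 |
| 0-30 | independent | 72.3 / 75.2 | 60.7-64.9 / 51.7-53.3 |
| 6-36 | independent | 88.9 / 75.2 | 71.9-78.0 / 51.7-53.3 |

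The stand-alone figures for independent misses can be checked by hand. With US at 0-30, a tumour has 0 to 5 US chances, so US alone is (0 + 0.6 + 0.84 + 0.936 + 0.974 + 0.990)/6 = 72.3%. MRI alone is (0.992 + 2 x 0.96 + 2 x 0.80 + 0)/6 = 75.2%.

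Adding versions with 20% of tumours prevalent at entry gives 16 scenarios. MRI is the better stand-alone programme in 12, and the scored table puts US ahead in 11 of those. The exception is a near tie (50.0 v 50.7). With 29 HCCs, the chance of a significant exact McNemar result favouring MRI is at most 1.6% in the eight scenarios without prevalent tumours.

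**Would same-day rounds alone repair it?** With misses and tools both independent, they recover 60% v 80%, using about 0.65 HCC-rounds per HCC (about 19 of 29). With persistent misses they do not, because US-only rounds have already removed US-visible tumours:

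- Nested, first same-day round per tumour: 3 + 2 x 0.4 = 3.8 units. US is 1.8/3.8 = 47% and MRI is (3 x 0.8 + 2 x 0.2)/3.8 = 74%.
- Independent tools, every same-day round with a tumour present: 3.8 + 4 x 0.08 = 4.12 units. US is 1.8/4.12 = 44% and MRI is (3 x 0.8 + 2 x 0.32)/4.12 = 74%.

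With 19 HCCs and discordance of 32% v 12% (independent tools), two-sided exact McNemar power is about 15%.

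**The case against.** **Fewer MRIs is the question being asked.** This stands for tumours arising after month 30. Within a 3-year window they are mainly the price of the yearly schedule that the Discussion defends, and should not be called bias. It does not cover tumours removed at a US-only visit before an MRI that was due. That removal undercuts the very offset, longer interval against higher sensitivity, on which the Discussion relies.

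**Exit cuts both ways.** It does. With US at 6-36 and independent misses, US falls from 88.9% to 72-78%. The net shift was still against MRI in every scenario.

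**The scoring rule is inferred.** This is fair. The article never states that these HCCs are MRI misses, and a fuller document could define the table. But schedule, exit rule, endpoint and test are all fixed here, and read per patient they give this result.

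**A reader might infer that the analysis always reverses the truth, or that a tally such as 72% v 52% shows reversal.** The documents do not support that. The endpoint compares programmes, not single examinations. Under the assumptions behind that tally, US at 6-36 with independent misses, US leads stand-alone as well (89% v 75%). Exit widens the gap but reverses nothing.

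**Conclusion.** The concern holds in this form: HCCs confirmed at US-only visits have no MRI result at detection, and the endpoint as worded counts them against MRI. The distortion can reverse the programme ranking. Stand-alone 60 v 67 becomes 60 v 47-51 (US at 6-36, persistent misses), and 72 v 75 becomes 61-65 v 52-53 (US at 0-30, independent misses). In other settings it only widens a real US lead: 89 v 75 becomes 72-78 v 52-53.

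Reversal is possible, not established. The size rests on onset timing, persistence of misses, dependence between the tools and the US start month, none of which the text gives. The mechanism itself rests only on stated rules.

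It is also tempting to conclude that a McNemar test confined to the same-day rounds would be a clean primary analysis. It would not: it answers a per-examination question instead of 6-monthly v yearly, and with persistent misses it favours MRI materially.

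**What to change.** The exit rule need not change. The change is to the endpoint and analysis wording, settled before the data are analysed:

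1. State that an HCC confirmed at a US-only visit has an unobserved MRI result and is not an MRI miss.
2. Report the 6-monthly v yearly comparison with best- and worst-case bounds for those HCCs. In the worked case they are 2 x 60/6 = 20% of HCCs, so MRI would be reported as 46.7% to 66.7% against US 60%.
3. Report tumours arising after the month-30 MRI separately, as a feature of the yearly schedule. Also show how many MRI-only detections ended later US rounds.
4. Base no claim of superiority for either tool on the unadjusted tally.
5. Add a paired McNemar analysis of the same-day rounds (months 6, 18 and 30) as a key supporting per-examination comparison, with month 6 shown alone.

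**Cost.** No new data are needed. The bounds widen the primary conclusion and may leave the ranking open, as they do in the worked case. The same-day analysis uses only about 65% of HCCs when misses are independent, has low power, and can favour MRI (about 44% v 74% with persistent misses). It supports the programme comparison and does not replace it.

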**Fig. 2 Fig2:**
[figure not shown]
Timeline for follow-up tests. US, ultrasonography; MRI, magnetic resonance imaging; CT, computed tomography; AFP, α fetoprotein; PIVKA-II, protein induced by vitamin K absence/antagonist II

#### Surveillance tests protocol

The liver US will be performed by experienced and board-certified abdominal radiologists. The standard liver US images, as designated by the National Cancer Center of Korea, will include the following [30]: an axial scan and longitudinal scan at the branching site of a main portal vein for evaluating right and left portal veins; scans of the caudate lobe, ligamentum venosum, hepatic artery, and extrahepatic bile duct; a long axis scan of the gallbladder; an axial scan of the inferior portion of the liver for the right, middle and left hepatic veins, and intrahepatic inferior vena cava; a longitudinal scan of the left hepatic lobe; an axial scan of left hepatic lobe for the left portal vein; an axial scan of the right hepatic lobe; and an intercostal scan at posterior mid-axillary line of the liver dome and right hepatic lobe [30].

The non-contrast liver MRI will be performed without using intravenous contrast media and with 3-T MR imaging units. The scan will include fat-suppressed sequences as follows: T2-weighted fast spin echo (FSE), fat-suppressed half-Fourier acquisition single-shot turbo spin-echo (HASTE), T1-weighted gradient echo (GRE) in- and opposed-phase images, fat-suppressed T1-weighted 3D GRE (VIVE or others), diffusion weighted image (DWI) with three diffusion weightings (b = 0, 50 and 500 s/mm^2^), and afferent diffusion coefficient (ADC) maps generated using b = 0 and 500 s/mm^2^. The liver MR images will be obtained with 5 mm thickness and no gap.

#### Imaging criteria for suspicious HCC

Suspicious findings for HCC on US are defined as follows: 1) newly developed hepatic nodule 1 cm or greater in size, and 2) the nodule does not exhibit typical findings associated with a simple hepatic cyst or typical hepatic hemangioma. A hepatic nodule satisfying two US criteria will be regarded as suspicious HCC. Even if a hepatic nodule is 1 cm or larger, a lesion that was previously diagnosed as benign or exhibits minimal interval change will be excluded.

Suspicious findings on MRI suggestive of HCC are defined as follows: 1) hepatic lesion with high signal intensity on T2-weighted image (T2WI), 2) fat-containing lesion on T1-weighted image (T1WI), 3) size increase greater than 100% in >6 months, and 4) diffusion restriction on diffusion weighted image (DWI). However, a hepatic lesion with bright signal intensity on T2WI that is suggestive of a simple hepatic cyst or hepatic hemangioma as well as a lesion that was previously shown to be a benign hepatic lesion will be excluded. The MRI of the liver will be interpreted by an experienced abdominal radiologist, who will be blinded to the results of the US examination.

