### Patient recruitment and selection

Patient recruitment was performed at six participating hospitals, including the Catholic University of Korea Seoul St. Mary’s Hospital, St. Vincent’s Hospital, Uijeongbu St. Mary’s Hospital, Seoul National University Hospital, Samsung Medical Center, and Korea University Guro Hospital. Patients with a diagnosis of liver cirrhosis who visited the medical center for HCC surveillance and had no previous diagnosis of HCC were included in this study.

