#### Sample size calculation

To calculate the number of subjects required to achieve statistical significance, the following assumptions were made:A crossover design study was planned for the two groups between US and non-contrast liver MRI.The incidence of cumulative hepatocellular carcinoma was assumed to be 15% for 3 years (5% per year) [28].The sensitivity of non-contrast liver MRI was assumed to be 80%, and the sensitivity of US was assumed to be 60% [27, 29].Type I error (α) = 5% and the power (1-β) = 80% were assumed.

A sample size of 192 patients was calculated to achieve 80% power for a difference in HCC detection of 60% for US and 80% for non-contrast liver MRI. The required sample size was 211 patients, assuming a drop-out rate of approximately 10%.

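### Lesion history can disqualify a nodule on US but not on MRI, so an HCC visible on US at an already known nodule can be scored as a US miss

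*Protocol article*

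**What the plan says.** All on the protocol article.

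- **Entry** (Patient recruitment and selection; Exclusion criteria). Cirrhotic patients attending for HCC surveillance who "had no previous diagnosis of HCC were included in this study". The exclusions concern diagnosed malignancy, pregnancy or breast-feeding, and refusal of consent. None concerns a known nodule whose nature is unresolved.
- **US** (Imaging criteria for suspicious HCC). Criterion 1 is a "newly developed hepatic nodule 1 cm or greater in size". Criterion 2 is the absence of typical cyst or hemangioma findings. Both are needed: "A hepatic nodule satisfying two US criteria will be regarded as suspicious HCC". In addition, "a lesion that was previously diagnosed as benign or exhibits minimal interval change will be excluded".
- **MRI** (same section). Four features are listed: T2 signal, fat on T1, "size increase greater than 100% in >6 months", and diffusion restriction. They are joined by 'and', without saying whether one or all must be present. Cyst-like and hemangioma-like lesions are removed, and "a lesion that was previously shown to be a benign hepatic lesion will be excluded". Neither newness nor stability is mentioned as a condition or an exemption.
- **Endpoint and test** (Endpoints; Statistical analysis). The primary endpoint compares the HCC detection rates of the two tests. The difference is tested by McNemar.

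**The concern.** In a paired comparison, each HCC should be scored on both tests by rules that differ only in what the tests can show. Here the rules also differ in how they treat a nodule's past. A radiologist may see a known, unresolved nodule at every US round and still be unable to call it, because it is not new or has changed little. The MRI reader faces no such bar. If the nodule proves to be HCC, US has a miss that reflects the scoring rule and not its ability to show the tumour.

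The US text also conflicts with itself. If criterion 1 already bars every known nodule, the exemption for minimal interval change has nothing left to remove. If a known nodule that has grown was meant to count, the text gives it no route to US-positive, because the exemption sentence only takes lesions away.

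At stake is the primary difference. Each such HCC that US would otherwise have detected shifts the net difference by one towards MRI. If MRI calls it, it moves from both-detected to MRI-only. If MRI does not, it moves from US-only to neither.

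**Working it through.** **1. Which known, not-shown-benign nodules are barred on US only?** Both rules are ambiguous, so there are four combinations.

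| US reading | MRI reading | Stable known nodule | Known nodule that has more than doubled |
|---|---|---|---|
| Strict: must be new | Not all four features needed | Barred on US only | Barred on US only |
| Strict: must be new | All four needed | Negative on both | Barred on US only |
| Lenient: growth may count | Not all four needed | Barred on US only | Callable on both |
| Lenient: growth may count | All four needed | Negative on both | Callable on both |

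Three of the four combinations leave an asymmetry, always against US. The fourth leaves none. The all-four reading would also stop MRI from calling any lesion without an earlier measurement, so it is probably not intended, but the article does not settle it.

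**2. Planning figures** (Sample size calculation): 192 patients, 15% cumulative incidence over 3 years, sensitivity 60% for US and 80% for MRI, alpha 5%, power 80%.

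The stated 192 can be reproduced with the McNemar normal approximation, n = (z_a√q + z_b√(q − d²))² / d². Here q is the discordant proportion and d the difference. With one-sided alpha 5% and no US-only detections, q = d = 0.20:

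- n = (1.645 × 0.447 + 0.842 × 0.400)² / 0.04 = 28.74 HCCs
- 28.74 / 0.15 = 191.6, so 192 patients

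Expected HCCs: 192 × 0.15 = 28.8. Expected detections: US 0.60 × 28.8 = 17.3, MRI 0.80 × 28.8 = 23.0. Planned net difference: 0.20 × 28.8 = 5.8.

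**3. Size under the strict US reading, with all such nodules barred on US and MRI unaffected.** Let f be the share of HCCs arising at known nodules not shown to be benign. The document does not give f; 5-20% is an assumption.

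- Scored US sensitivity = 0.60 × (1 − f)
- Lost US detections = f × 0.60 × 28.8

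| f | HCCs at such nodules | Lost US detections | Scored US sensitivity | Apparent MRI − US gap |
|---|---|---|---|---|
| 0 | 0 | 0 | 60% | 20 points |
| 5% | 1.4 | 0.9 | 57% | 23 points |
| 10% | 2.9 | 1.7 | 54% | 26 points |
| 20% | 5.8 | 3.5 | 48% | 32 points |

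**4. Effect on the test.** This illustration uses 29 HCCs, independent reads and an exact two-sided McNemar test at 5%. Entries are the chance of a significant result favouring MRI.

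| True sensitivity, US / MRI | f = 0 | 5% | 10% | 20% |
|---|---|---|---|---|
| 80% / 80% | 1.1% | 2.7% | 5.7% | 17.7% |
| 70% / 70% | 1.2% | 2.5% | 4.6% | 12.6% |
| 60% / 80% | 27% | 35% | 44% | 63% |

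For small f the inflation is modest; at 20% it is not.

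**The case against.** The strongest case against has five parts.

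- **MRI positivity is not automatic.** This stands. A reader might infer that an HCC at a known nodule is US-negative and MRI-positive by rule. The text makes it only eligible to be MRI-positive, subject to the listed features. For a stable nodule even that fails if all four features are required.
- **The strict US reading makes the next sentence redundant, so growth was probably meant to count.** This stands in part. The exemption would have work to do if, for example, a known nodule newly reaching 1 cm could qualify. The affected group is then only known nodules that are still minimally changed, and the figures above are too large. But the article does not say so, and the two sentences remain unreconciled.
- **The share f has no support in the document.** This stands. The range is illustrative.
- **Not recalling stable lesions may be part of the US strategy under test.** This is a fair defence of the referral rule. It does not explain why the same history is ignored on MRI when the two are compared head to head.
- **The article is condensed.** The full protocol may fix the reference examination for newness, and its silence here is not held against the plan. The difference between the two rules, and the conflict within the US rule, are in the printed text.

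**Conclusion.** The asymmetry is real and runs one way: where it operates, it favours MRI. Eligibility lets the relevant patients in, and lesion history can then turn a US-visible HCC into a scored US miss. For a stable nodule this depends on the four MRI features not all being required.

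The size is unknown. With f of 5-20% and every such nodule barred on US, the loss is about 0.9 to 3.5 US detections, against a planned net difference of about 6. It is smaller if growing known nodules may be called on US.

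A reader might compare the number of HCCs at such nodules (about 3 to 6 at f of 10-20%) with the planned difference and infer that the rule could produce the whole effect. The documents do not support that: only the share that US would have detected is lost, 1.7 to 3.5 over that range. The point deserves correction, but it does not show that the primary result would be an artefact.

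**What to change.** 1. Reconcile the two US sentences, and state whether one or all of the four MRI features are required.
2. For endpoint scoring, state one lesion-history exemption for both modalities: previously shown to be benign. This concerns scoring only and changes neither referral nor care.
3. Record in the eCRF every nodule of 1 cm or more seen on US that is not a cyst or hemangioma, whether new or not.
4. Prespecify a sensitivity version of the McNemar comparison that either counts a later-confirmed HCC at such a recorded site as seen on US, or omits HCCs at nodules known at entry.
5. Report that version beside the primary analysis, not in its place. Crediting US with nodules it did not call, some confirmed only because MRI prompted the CT, could tilt the comparison towards US.

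An added entry exclusion for unresolved nodules would come too late, since the article reports recruitment in the past tense.

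The cost is one extra eCRF field per US examination. In the sensitivity version the MRI advantage may look smaller and US false positives more frequent.
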